### 2.6. Prior and Concomitant Illnesses and Treatments

Relevant additional illnesses present at the time of informed consent are regarded as concomitant illnesses and will be documented in the patient chart. Abnormalities which appear for the first time or worsen (intensity and frequency) during the trial are adverse events (AEs) and must be documented on the appropriate pages of the case report form (CRF). Relevant additional treatments administered to the patients on entry to the trial or at any time during the trial are regarded as concomitant treatments and must be documented on the appropriate pages of the CRF. During radiation therapy, medication required for concomitant illnesses (i.e., hypertension, thyroid disease, hyperlipidemia, etc.) should be applied. Concomitant medication should be discussed with the principal investigator on an individual basis. The concomitant systemic therapy, as indicated by the national guidelines, represents a standard of care and is not a part of the study protocol. Additional concomitant systemic therapy or other anti-tumor medication are also not part of the study protocol and are only allowed if in accordance with the treating radiation oncologist.

### 2.7. Statistical Analysis

The primary endpoint will be analyzed in the safety population. The toxicity rate will be calculated using a 90% Wilson-type confidence interval. No imputation of the primary endpoint will be conducted. Further analyses of the primary endpoint will be carried out in the ITT and PP population.

Analyses of secondary endpoints will be descriptive and will include the calculation of appropriate summary measures of the empirical distributions (continuous variables: mean, standard deviation, median, interquartile range, minimum, and maximum; categorical variables: frequencies and percentages). 

Time-to-event endpoints will be visualized by means of Kaplan–Meier plots and/or cumulative incidence functions. Secondary efficacy endpoints will be assessed in the ITT population, with further analyses conducted for the PP population. 

The method of Kaplan and Meier will be used to estimate the distributions of PFS and OS. Additionally, 95% log–log-type confidence intervals will be given for the Kaplan–Meier estimates.

Distant and regional tumor control will be assessed via cumulative incidence functions, taking the competing event death into account. The 95% confidence intervals for the cumulative incidence will be given.

QoL, as well as tumor size and other MRI-based continuous parameters, will be summarized by the mean, standard deviation, median, minimum, and maximum, and will be plotted based on time. The change from baseline over time will be examined descriptively. The safety analysis will comprise a tabulation and summary of adverse and serious adverse events and will be based on the safety population. The relative frequency of adverse and serious adverse events are summarized along with two-sided confidence intervals with a Wilson score of 95%.

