## 2. Methods

### 2.1. Study Design

The trial will be performed as a prospective single-arm phase-II proof-of-concept study.

The planned recruitment time for a total of 40 patients is 24 months. The inclusion and exclusion criteria are described in Table 1 and Table 2.

EBRT will be planned based on pre-therapeutic MRI and planning CT, and will consist of 25–28 fractions of 1.8 Gy leading to a total dose of 45–50.4 Gy using intensity-modulated radiotherapy (IMRT). A simultaneous integrated boost of 2.1–2.2 Gy will be applied to eventual lymphatic node metastases, leading to a boost plan dose of 55.0–58.8 Gy. Concurrent platinum-based chemotherapy (e.g., cisplatin 40 mg/m^2^ weekly; aim: 5–6 cycles) will be applied during EBRT according to current international and German guidelines [17]. Target volume delineation for EBRT was adapted from Lee et al. [18], as well as from the consensus guidelines of the Radiation Therapy Oncology Group [19]. Furthermore, an adapted version of the recently introduced internal target volume (ITV) concept of the EMBRACE-II study will be used to account for intrafractional organ motion [20]. 

Gross tumor volume (GTV): macroscopic contrast-enhanced tumor in the planning MR and, if definable, in the planning CT.Clinical target volume (CTV):■CTV 1: GTV, cervix, and uterus.■CTV 2: paravaginal/parametrial tissue; proximal half of the vagina (proximal two-thirds if infiltrated).■CTV 3: internal/external/common iliacal, as well as presacralic (S 1/2), lymphatic drainage area (including surgical clips and lymphoceles); cranial border: aortic bifurcation; caudal border: caput femoris (external iliacal) or cranial vaginal end (internal iliacal).Depending on the planning CT and MRI scan, CTV 1 and CTV 2 will be combined and adapted to form an ITV, which accounts for the organ motion during the adaptation process.A margin of 5 mm will be added to the ITV and CTV 3 to generate the planning target volume (PTV).

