All patients will receive a pre-EBRT and (during EBRT) a pre-BT pelvic MRI scan for diagnostic and treatment planning purposes (contrast-enhanced), as well as once weekly during CCRT for image guidance (non-contrast-enhanced) in treatment positions. Patients will be immobilized and shuttled (Symphony™ Patient Transport System) from the 3T MRI scanner (VIDA, Siemens) to the ETHOS system, which is located in the same vault. The shuttle system is MR-compatible and utilizes low-friction air bearing to transition patients from one modality to another, eliminating the need to manually lift the patient. MR coil fixation systems from QFix allow for the alignment of MR coils without touching or deforming the patient’s surface. Furthermore, MRI will be regularly performed during follow-up visits (contrast-enhanced).

Patients will be scheduled for study visits in the middle of CCRT and at the end of CCRT. As per institutional clinical standards, patients receive their first follow-up study visit five weeks after the end of brachytherapy, which functions as a baseline for subsequent visits every three months after the end of radiotherapy and then every three to six months up to two years of follow-up. Follow-up visits include a clinical assessment, as well as a contrast-enhanced MRI, of the pelvis. The respective study visits also include an analysis of quality of life (using EORTC QLQ C-30 and EORTC QLQ CX-24 questionnaires). Baseline symptoms and toxicities will be assessed according to CTCAE V5.0. The flowchart of the AIM-C1 study is found in Figure 1. 

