### 2.3. Sample Size Calculation

This is an exploratory trial which aims to provide a first reliable rate estimate of the primary endpoint, serving as a starting point for subsequent potential randomized trials, defined as the occurrence of treatment-related bowel or bladder CTCAE V5.0 toxicity (G2 or higher) assessed at the first 3 months after the beginning of treatment. 

Bladder toxicity of grade 2 (G2) or higher (frequency/urgency, incontinence, spasm, stenosis, cystitis, bleeding, fistula, etc.) was described to be 6.1% after three months since the beginning of the CCRT for cervical carcinoma in the EMBRACE study [21]. Overall, bowel morbidity of G2 or higher (diarrhea, flatulence, incontinence, stenosis/stricture fistula, etc.) was reported to be approximately 4% at three months [22]. Thus, the G2 or higher bowel and bladder toxicity is approximately 10% with the conventional irradiation technique.

With a sample size of *n* = 40 patients, and assuming that a G2 or higher toxicity rate of 8% can be achieved through daily adaptation and weekly MRI guidance, the 90% Wilson score rate confidence interval will be [3.3%, 18.0%] with a width of 14.7 percent points, thus illustrating the evidence that can be gained with our trial. Our primary goal is to provide a first estimate of the toxicity rate for experimental treatment. Sample size calculation was carried out using PASS v16.0.3. 

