### 2.4. Study Objectives

The purpose of this phase-II proof-of-concept study is to reduce irradiation-induced toxicity and morbidity in cervical cancer patients through daily CBCT-based and AI-supported adaptation under weekly MR guidance. External beam radiotherapy itself, concomitant chemotherapy, and the subsequent brachytherapy are performed according to national guidelines and internal standard-operating procedures (SOPs) and are therefore clinical routine.

The primary endpoint is defined as the occurrence of treatment-related bowel or bladder CTCAE V5.0 toxicity (G2 or higher) within the first 3 months. 

The secondary objectives include an evaluation of treatment efficacy and patient survival, as well as changes in quality of life. This also includes local and distant tumor control, according to RECIST v1.1, as well as progression-free survival and overall survival. Furthermore, the clinical feasibility of MR guidance, especially plan adaptation using the AI-based ETHOS system, will be studied. In addition, morphological, functional, and motional changes in MRI will be compared to those in CT scans. Finally, secondary objectives encompass a collection of treatment plans and irradiation parameters, as well as imaging data and quality assurance results for further analysis and the planning of follow-up projects, including how often the adapted plan was chosen, the dosimetric benefits of adaptation, dosimetric comparison with other radiotherapy techniques, the analysis of plan robustness, the evaluation of AI-based adaptation, the analysis of image registration algorithms, as well as the assessment of fraction dose accumulation methods.

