## 3. Discussion

CCRT is a well-established curative treatment concept for locally advanced cervical cancer patients, albeit the irradiation dose is conventionally barely adjusted to the individual patient [2]. Nearby pelvic OAR (like the bowel and the bladder, as well as the uterus itself) are known to show high-position variability over time [11,12]. To account for this variability, when using conventional techniques, large safety margins need to be applied, leading to an irradiation dose exposition of surrounding radiosensitive organs at risk (OARs), and hence toxicity and morbidity [5]. Bowel and bladder morbidity after pelvic irradiation often persist for years, have a dramatically negative impact on quality of life, and even become further important in times of increasing long-term cancer survivorship [4,6,23].

The ETHOS radiotherapy device offers an AI-supported daily treatment plan adaptation and thereby reduces the amount of unnecessary irradiated healthy tissue [24]. 

The first results in cervical cancer patients demonstrated the feasibility and dosimteric benefits of the ETHOS radiotherapy system [25,26,27,28]. However, these studies were partly from in silico trials, and clinical results are still missing. 

As one of the few centers worldwide, we can combine the latest radiotherapy device with weekly offline MR-based adaptation in treatment positions, including functional imaging. MR-guided radiotherapy with its superior soft-tissue contrast is believed to facilitate the precise detection of the current tumor dimension. This is especially important for cervical cancer, which often shrinks by up to 60–80% over the radiotherapy period, underlining the potential for adaptive treatment strategies [29]. There is growing evidence for the utilization of functional MRI in gynaecological malignancies [30]. Early tissue changes, visualized by MRI scans during the chemoradiotherapy course, have the potential to predict tumor responses and late toxicity, and thus may be used to determine the optimal individual irradiation dose [31,32,33]. 

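### Crude adverse event proportions would understate bowel and bladder toxicity arising after 3 months if two-year follow-up is incomplete; a cumulative incidence estimate should be added

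*Protocol article*

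**What the plan says.** All references are to the protocol article.

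- **Adverse events, Section 2.7 (Statistical Analysis):** "The relative frequency of adverse and serious adverse events are summarized along with two-sided confidence intervals". The intervals are 95% Wilson score intervals and the population is the safety population. No other method is named for toxicity beyond the primary endpoint.
- **Primary endpoint, Section 2.4 (Study Objectives):** "treatment-related bowel or bladder CTCAE V5.0 toxicity (G2 or higher) within the first 3 months".
- **Follow-up, Section 2.1 (Study Design):** after the early visits, patients are seen "every three to six months up to two years of follow-up". Recruitment is staggered: "The planned recruitment time for a total of 40 patients is 24 months".
- **Withdrawal, Section 2.5:** data collection stops at withdrawal. Earlier data are kept only with the patient's consent and are otherwise deleted. The same section asks for final-visit examinations where possible and for follow-up of adverse events still ongoing at withdrawal.
- **Other outcomes, Section 2.7:** Kaplan–Meier is used for PFS and OS. For tumour control, "Distant and regional tumor control will be assessed via cumulative incidence functions, taking the competing event death into account".
- **Background, Section 3 (Discussion):** "Bowel and bladder morbidity after pelvic irradiation often persist for years".

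**The concern.** A crude proportion divides patients with an event by all patients in the population. A patient who leaves at month 9 without an event, and whose data are kept, then counts as event-free to month 24. The Wilson interval gives that patient the same weight as one seen for the whole period. Within a 3-month window this hardly matters. Over two years it can, and the error runs downward, which favours the adaptive technique.

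Section 2.7 already handles incomplete follow-up for survival and tumour control, but names no such method for toxicity, although reducing toxicity is the trial's stated purpose. At stake is a descriptive safety figure that a later randomised trial might use for planning.

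**Working it through.** **1. The plan's own interval.** For 40 patients and an assumed early toxicity rate of 8%, Section 2.3 reports a 90% Wilson interval of 3.3% to 18.0%, 14.7 points wide. The Wilson limits are [p + z²/2n ± z·√(p(1−p)/n + z²/4n²)] / (1 + z²/n). With p = 0.08, n = 40 and z = 1.645:

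- centre: (0.08 + 0.0338)/1.0677 = 0.1066
- half-width: 1.645 × √(0.00184 + 0.000423)/1.0677 = 0.0733
- limits: 3.33% to 17.99%, width 14.66 points. The stated figure reproduces.

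**2. Interval for the adverse event tables.** For 4/40 with z = 1.96, the same formula gives 4.0% to 23.1%, a width of about 19 points.

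**3. Crude proportion against cumulative incidence.** The article gives no late-toxicity, loss or death rate at 24 months, so all three are assumptions. Let F, L and D be the 24-month probabilities of late toxicity, loss to follow-up and death, each acting alone. Assume constant and independent hazards h = −ln(1−F)/24, l = −ln(1−L)/24 and d = −ln(1−D)/24. Then:

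- crude = h/(h+l+d) × (1 − exp(−24(h+l+d)))
- cumulative incidence with death competing = h/(h+d) × (1 − exp(−24(h+d)))

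Check with F = L = 20% and D = 0: h = l, so crude = ½ × (1 − 0.8 × 0.8) = 18.0%, against a true 20.0%. The shortfall is 2.0 points.

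For F from 10% to 30% and D from 0% to 20%:

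| Loss by 24 months | Shortfall (points) | Relative |
|---|---|---|
| 0% | 0 | 0 |
| 5% | 0.2 to 0.7 | about 2% |
| 10% | 0.4 to 1.4 | about 5% |
| 20% | 0.9 to 2.9 | about 10% |
| 30% | 1.4 to 4.5 | about 15% |

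The zero row holds whatever the death rate: death alone creates no gap between the crude proportion and a competing-risk estimate. In patients, 10% loss hides 0.4 to 1.4 points × 40 = about 0.2 to 0.6 of a patient. At 30% loss it is 1.4 to 4.5 points × 40 = about 0.6 to 1.8 patients.

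**4. Analysis before everyone reaches 24 months.** With no loss or death and follow-up spread evenly from a to 24 months, crude = 1 − [exp(−ha) − exp(−24h)]/[h(24−a)]. For a = 12, F = 10% gives 7.6% (2.4 points low) and F = 30% gives 23.4% (6.6 points low). For a = 6, F = 25% gives 16.3% (8.7 points low, 35% relative). The article states no such early cut, so these figures show only what one would do.

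**The case against.** The strongest objection is that the sentence describes general tabulation of all adverse events. It says nothing specific about the period after 3 months, late toxicity, or bowel and bladder. Late toxicity is not among the objectives in Section 2.4, so a different method from tumour control, which is a listed endpoint, is no contradiction. The general sentence in Section 2.7 on displaying time-to-event endpoints does not exclude toxicity, and the full protocol or analysis plan may say more. Much of this stands: the article is not shown to report late toxicity only as crude rates. What remains is that the one method it fixes for adverse events does not fit outcomes collected over unequal follow-up.

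Three stronger readings are tempting but not supported:

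- **Late toxicity will be understated.** This is conditional. With complete follow-up the bias is zero, and no loss rate is given. The 24-month recruitment period does not itself imply that patients are cut off early. Withdrawn patients who refuse use of their data are deleted and leave the denominator, so they are not counted as event-free.
- **Late toxicity is the trial's main rationale.** Persistent morbidity is prominent in the background, but the primary endpoint and the sample size concern the first 3 months.
- **A crude rate breaks comparability with the cited 15.3%.** That figure is an actuarial 5-year rate of grade 3 or higher toxicity. A 24-month cumulative incidence would differ from it in horizon too.

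The follow-up of ongoing adverse events after withdrawal covers events already present. It does not capture new ones.

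**Conclusion.** The point holds as a conditional, minor one. A crude proportion with a Wilson interval is the wrong summary for bowel or bladder toxicity arising after 3 months if follow-up to two years is incomplete, whether through withdrawal with data kept, loss to follow-up, or analysis before all patients reach 24 months.

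Under constant, independent hazards and an assumed true rate of 10% to 30%, losses of up to 30% move the estimate by at most about 4.5 points, well inside the sampling error with 40 patients. An early data cut could move it further, but none is stated. If loss is related to toxicity, these figures do not apply. The primary endpoint, its 90% interval and the sample size are unaffected. The case for change is that the better method is already in the plan and costs little.

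**What to change.** In Section 2.7, keep the crude adverse event tables and add a descriptive safety analysis along these lines:

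> Bowel or bladder toxicity arising after the 3-month window will be estimated, for grade 2 or higher and for grade 3 or higher, by a cumulative incidence function in the safety population. Death is the competing event, and patients without an event are censored at their last toxicity assessment. Estimates with 95% confidence intervals will be given at 12 and 24 months.

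The text should also fix the time origin, because the primary window counts from the start of treatment while follow-up visits count from the end of radiotherapy. It should say how toxicity carried over from the first 3 months is treated. No new endpoint with a formal claim is needed.

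**Cost:** one extra analysis by a method already specified for tumour control. Onset dates, or the date of the visit at which the event was first detected, must be available from the case report form; Section 2.6 says that adverse events are documented there but does not mention dates. With visits up to six months apart, timing will be approximate. Intervals at 24 months will be somewhat wider than the Wilson intervals, reflecting the smaller number still under observation.

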### 2.8. Ethical Aspects

This study is carried out in accordance with the Declaration of Helsinki and received approval by the Ethics Committee of the Medical Faculty of the University of Heidelberg (S-466/2023 date of approval: 27 September 2023).

## 3. Discussion

CCRT is a well-established curative treatment concept for locally advanced cervical cancer patients, albeit the irradiation dose is conventionally barely adjusted to the individual patient [2]. Nearby pelvic OAR (like the bowel and the bladder, as well as the uterus itself) are known to show high-position variability over time [11,12]. To account for this variability, when using conventional techniques, large safety margins need to be applied, leading to an irradiation dose exposition of surrounding radiosensitive organs at risk (OARs), and hence toxicity and morbidity [5]. Bowel and bladder morbidity after pelvic irradiation often persist for years, have a dramatically negative impact on quality of life, and even become further important in times of increasing long-term cancer survivorship [4,6,23].

The ETHOS radiotherapy device offers an AI-supported daily treatment plan adaptation and thereby reduces the amount of unnecessary irradiated healthy tissue [24]. 

The first results in cervical cancer patients demonstrated the feasibility and dosimteric benefits of the ETHOS radiotherapy system [25,26,27,28]. However, these studies were partly from in silico trials, and clinical results are still missing. 

As one of the few centers worldwide, we can combine the latest radiotherapy device with weekly offline MR-based adaptation in treatment positions, including functional imaging. MR-guided radiotherapy with its superior soft-tissue contrast is believed to facilitate the precise detection of the current tumor dimension. This is especially important for cervical cancer, which often shrinks by up to 60–80% over the radiotherapy period, underlining the potential for adaptive treatment strategies [29]. There is growing evidence for the utilization of functional MRI in gynaecological malignancies [30]. Early tissue changes, visualized by MRI scans during the chemoradiotherapy course, have the potential to predict tumor responses and late toxicity, and thus may be used to determine the optimal individual irradiation dose [31,32,33]. 

In summary, daily adaptive cone beam CT (CBCT)-guided radiotherapy at the ETHOS offers the opportunity to significantly optimize treatment strategies regarding target coverage and toxicity. The additional integration of weekly MRI in treatment positions potentially allows for the functional non-invasive assessment of tissue perfusion, hypoxia, or cellular density. These data could be used for treatment adaptation and the assessment of early tissue changes. Up to now, there are only few data about daily adaptive CCRT in locally advanced cervical cancer. The aim of the current trial is therefore to evaluate the potential of daily adaptive CCRT in cervical cancer and analyze the benefit of the additional integration of high-resolution MRI in treatment positions for toxicity and response assessment. Our study will serve as a starting point for a potential subsequent randomized trial.

## Figures and Tables

**Figure 1 jcm-13-00957-f001:**
[figure not shown]
Flowchart of the AIM-C1 study.

**Table 1 jcm-13-00957-t001:** Inclusion criteria of the AIM-C1 study.

Biopsy-proven cervical cancer, including squamous cell carcinoma, adenocarcinoma, or adeno-squamous cell carcinoma FIGO-stage IB/IIA (if medically inoperable or ≥3 risk factors *), IIB, IIIA, IIIB, and IIIC1 (staging: pelvic MRI and thoracoabdominal CT) Indication and eligibility for definitive chemoradiotherapy, including brachytherapy discussed in an interdisciplinary tumor board Karnofsky performance score ≥ 70% 18–80 years of age Capacity of the patient to consent to participation in the study Patient-informed consent

* risk factors: L1, V1, deep stromal invasion, tumor size ≥ 4 cm, G3.

**Table 2 jcm-13-00957-t002:** Exclusion criteria of the AIM-C1 study.

FIGO-Stage IIIC2 and IV
Paraaortic Lymphatic Node Metastases
Small-cell neuroendocrine cancer, melanoma, and other rare cancers of the cervix Previous radiotherapy of the pelvic region Previous total or partial hysterectomy Contraindications against performing contrast-enhanced MRI scans (pacemakers, other implants making MRI impossible, and allergies to gadolinium (GD)-based contrast agents) Claustrophobia Pregnant or lactating women Other primary malignancies within 5 years before, except carcinoma in situ of the cervix and basal cell carcinoma of the skin Patient is enrolled in another study, which could influence the outcome of the presented study

